### Participant timeline

Study timeline is depicted in Fig. 2. Before starting the intervention, a 2-week run-in period will be implemented during which participants will be asked to complete a 3-day dietary record (two weekdays and a weekend day). A qualified nutritionist will analyze all 3-day dietary records using the Metadieta software application (Me.Te.Da., San Benedetto del Tronto, Italy), which is linked to the Italian database of food composition (INRAN/IEO, 2008). Then, participants will be randomly divided into two groups, each assigned to the intervention or control group. There will be two clinical evaluations of the study population: at the beginning (*Time 0*) and at the end of dietary interventions (*Time 1*).

**Fig. 2 Fig2:**
[figure not shown]
Organization of the intervention study

### Sample size

The calculation of the sample size and statistical power was measured considering the 80% probability to show as statistically significant (*p* < 0.05) a 1.4% weight reduction difference between the intervention group and the control group, with a standard deviation of 0.4% and a loss at follow-up of 22%. This calculation was derived from a study in the literature that evaluated the difference between a diet adapted to the chronotype and a control diet in overweight/obese subjects [16]. The minimum number of subjects to be recruited to obtain reliable results with a statistical power of 0.8 (beta) and 0.05 (alpha) is 54 participants per group. Dropouts will be included in the intention-to-treat analysis, which includes all participants initially randomized. Per-protocol analyses, focusing on those who complete the trial without major deviations, will also be conducted to provide a comprehensive perspective on treatment efficacy.

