### Participants

A total of 150 overweight and obese females and males aged between 18 and 65 years with a body mass index (BMI) ≥ 25 kg/m^2^ will be included in the study. Exclusion criteria will be the presence of chronic illnesses or unstable conditions that could interfere with the dietary intervention (e.g., cancer, kidney or liver disease, inflammatory bowel disease, cognitive decline, and psychiatric disease); drug therapies that could interfere with the effectiveness of the dietary intervention (e.g., use of corticosteroids, and anti-diabetic drugs); pregnancy or intention to become pregnant in the next 12 months; breastfeeding; current or recent (last 3 months) adoption of a low-calorie diet.

Before starting any research activities, including the initial run-in period, the study investigators will obtain written informed consent from each participant. All subjects must voluntarily agree to participate and will be free to withdraw from the study at any time. Study participants will also be asked for written informed consent to keep the biological samples for future research and to publish the data anonymously.

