One of the strengths of this study protocol is the randomized controlled trial design, which allows for rigorous assessment of causal relationships. Randomization helps minimize confounding factors and improves internal validity, enabling us to draw more reliable conclusions about the effects of chronotype-adapted diet. In addition, the inclusion of comprehensive outcome measures, including weight loss, body composition, metabolic markers, and gut microbiota composition, provides a holistic understanding of the potential impacts of the dietary intervention. Despite its potential contributions, this study has several limitations that should be acknowledged. Firstly, the study duration and sample size may limit the generalizability of the findings. Secondly, although the chronotype-adapted diet may demonstrate greater efficacy, the extent remains uncertain. Our study was designed with the statistical power to demonstrate a minimum difference of at least 1.4% between intervention and control groups, a value determined by standard practices for sample size estimation in power analysis. However, it is noteworthy that this chosen value may not necessarily have clinical relevance. Additionally, our ability to predict the sustainability of weight loss beyond the study duration is limited due to the exploratory nature of the research. Given the typical decline in diet adherence after the initial 6 months, uncertainties persist regarding long-term effects. Finally, the reliance on self-reported data, such as chronotype assessment and dietary intake, introduces the possibility of recall bias. If this trial leads to highly relevant results, future studies could incorporate objective measures such as actigraphy and dietary biomarkers, which are more accurate but have much higher costs.

In conclusion, the results obtained from the implementation of this trial have the potential to advance our understanding of the complex interactions between chronotype, diet, and health outcomes. By providing evidence of personalized dietary interventions based on an individual’s circadian preferences, this research may contribute to the development of innovative dietary approaches to optimize the management of overweight and obesity, while also improving the risk profile of these patients.

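### The sample-size figures contradict each other: a 1.4% difference with an SD of 0.4% needs about 3 participants per group for 80% power, not 54

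*Protocol article*

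**What the plan says.** The Sample size section of the protocol article gives a nearly complete set of inputs: 80% power, p < 0.05, a "1.4% weight reduction difference between the intervention group and the control group, with a standard deviation of 0.4" per cent, and "a loss at follow-up of 22" per cent. It takes them from one published study of a chronotype-adapted diet. From these it concludes that the minimum number to recruit "with a statistical power of 0.8 (beta) and 0.05 (alpha) is 54 participants per group".

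The Study design and Statistical analysis sections supply the rest: 1:1 allocation, superiority, and an independent-samples t-test on change between groups. Whether the test is one- or two-sided is not stated.

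The Participants section sets the planned enrolment: "A total of 150 overweight and obese females and males aged between 18 and 65 years". The Discussion repeats the power claim as a property of the design: "Our study was designed with the statistical power to demonstrate a minimum difference of at least 1.4% between intervention and control groups".

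**The concern.** A between-group difference three and a half times the SD is very large, and a two-arm comparison of means would detect it with a handful of people. A requirement of 54 per group belongs to a much smaller standardised difference, so at least one of the printed difference, SD and n is not the figure that was used.

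What is at stake is the meaning of the power statement for the primary outcome. The SD determines what 150 recruits can detect, and the only SD printed cannot be squared with the sample size printed beside it. A reader therefore cannot verify the 80% or the Discussion's claim about 1.4%. A later trial that borrowed 0.4% as the SD of weight change could plan a study that is far too small.

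**Working it through.** **Inputs.** Difference δ = 1.4, SD σ = 0.4, power 0.80, α = 0.05, loss 22%, stated n = 54 per group (all from Sample size). 1:1 allocation is from Study design and the independent t-test from Statistical analysis. Planned enrolment of 150 is from Participants. A two-sided test is my assumption; one-sided is also tried below.

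**Step 1: try to reproduce 54.** The standardised difference is 1.4 / 0.4 = 3.5.

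Normal approximation: n = 2(1.960 + 0.842)² / 3.5² = 15.70 / 12.25 = 1.28, so 2 per group.

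Exact t-test (noncentral t with noncentrality 3.5 × √(n/2)):

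| n per group | Power |
|---|---|
| 2 | 47.7% |
| 3 | 88.6% |
| 4 | 98.2% |

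So 3 per group suffice. After 22% loss, 3 / 0.78 = 3.85, so 4 per group. The stated 54 is not reproduced.

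**Step 2: variants.**
- A one-sided test at 80% or 90% power still gives 2 to 3 per group.
- A two-sided test at 90% power gives 4, or 4 / 0.78 = 5.1, so 6 after loss.
- Swapping the two inputs (difference 0.4, SD 1.4) gives 193 per group before loss and 248 after.
- At SD 0.4, power with 54 or with 42 evaluable per group is effectively 100%.

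No variant gives 54. The article states no clustering, multiplicity or subgroup requirement that would raise the number.

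**Step 3: the SD that 54 would imply.** Hold δ = 1.4 and 80% power, and solve σ ≈ 1.4 × √(n/2) / 2.802, then refine with the exact t-test.
- 54 recruited, loss included: 54 × 0.78 = 42.1 completers. σ ≈ 1.4 × √21 / 2.802 = 2.29; exact t 2.26.
- 54 completers: σ ≈ 1.4 × √27 / 2.802 = 2.60; exact t 2.57.

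This step is conditional: it takes 1.4% and 54 as correct and lets only the SD move.

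**Step 4: the planned enrolment.** 150 × 0.78 = 117 completers, about 58 per arm. For 80% power at δ = 1.4, exact t allows an SD of at most 2.67. Power for 1.4% with 58 per arm:

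| SD of percent weight change | Power | Status of the SD |
|---|---|---|
| 2.26% | 91% | back-solved, 54 recruited |
| 2.57% | 83% | back-solved, 54 completers |
| 2% | 96% | assumption |
| 3% | 70% | assumption |
| 4% | 46% | assumption |
| 5% | 32% | assumption |

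**Step 5: one possible explanation, not established.** If 0.4 were a per-arm standard error from m participants, then SD = 0.4 × √m. Reaching 2.26 to 2.57 needs m = (2.26/0.4)² ≈ 32 to (2.57/0.4)² ≈ 41 per arm. The article does not give the source study's size, so this is only something to check.

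**The case against.** The strongest defence is that the inconsistency does the trial no visible harm. Read literally, an SD of 0.4% makes 54 per group far more than enough. If the SD is instead back-solved from 54, the 150 planned recruits give about 91% or 83% power for 1.4%, above the 80% target on either reading. What a null result rules out will be read from the confidence interval, not from the planned power. The Discussion also already concedes that 1.4% may lack clinical relevance. Most of this stands. It limits the consequence, but it does not make the printed figures agree.

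Some stronger readings are tempting and not supported:
- **That the SD is the wrong figure, by a factor of about six.** The back-solve assumes that the difference and n are right. The documents show only that the three cannot all hold.
- **That the trial is underpowered.** The low powers in the table come from assumed SDs of 3% to 5%, for which the article offers no evidence.
- **That 150 contradicts 54 per group.** The 54 is given as a minimum, and 150 exceeds 2 × 54 = 108.
- **That the handling of loss is left open.** The 22% is listed among the inputs, and 54 is described as the number to recruit, so the plain reading is that loss is included. The completers reading is carried here only as a bound.

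Labelling power as beta is a clerical slip, since the 80% is stated plainly. Nor is this the kind of detail an article leaves to a fuller document: the article prints the inputs and the result, and they conflict.

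**Conclusion.** The point holds as an internal inconsistency. The stated difference, SD, power and α lead to about 3 per group (about 4 after loss), and the article says 54. Sidedness, 80% or 90% power, and the dropout adjustment do not close the gap.

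If 1.4% and 54 are kept, the SD must have been about 2.3% (54 recruited) or about 2.6% (54 completers). Which figure is wrong cannot be settled from the documents, because the source study is not at hand. The power claim repeated in the Discussion is therefore unverifiable as printed; it is not shown to be false. The result rests on the t-test and 1:1 allocation that the article itself names, with a two-sided test assumed for the exact figures.

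**What to change.** 1. Go back to the source study and reconcile the difference, the SD and n. Establish in particular whether 0.4% is the SD of individual percent weight change or another quantity, such as a standard error.
2. Print the reconciled inputs with the resulting n in Sample size, including the sidedness of the test.
3. Using the reconciled SD, restate the power for 1.4%, or the smallest detectable difference, for 150 recruits and about 58 completers per arm. The benchmark is that 80% power for 1.4% requires an SD of at most about 2.67%.
4. Align the power sentence in the Discussion with the result.

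This costs a recheck of one reference and a few sentences of protocol text. Recruitment, conduct and analysis need not change. The one downside is that the restated power may be less favourable than the article now suggests.

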### Recruitment

Female and male participants will be recruited using advertisements on local media, newspapers, social media, official papers, and websites. We will also recruit from our existing database of participants and friends or relatives of the hospital and university staff.

### Assignment of interventions: allocation

A web-based online randomization procedure will be used to generate the allocation sequence. No adaptive randomization procedures will be performed. The random assignment sequence will be produced and managed by an investigator who will not participate in the recruitment of participants. The order of assignment will be kept secret from the experimenters who will enroll participants or assign interventions. The group assignment will be presented on a folded sheet of paper in a sealed envelope.

### Assignment of interventions: blinding

Blinding of study participants and nutritionists will not be possible because of the obvious differences between intervention diets; however, outcome measures cannot be easily influenced by the observer. In addition, study personnel who will enroll participants, data collectors, outcome assessors, and data analysts will be blinded to the treatment assignment, and a researcher from outside the research team will enter the data into the database.

### Data collection and management

Assessments and data collection at baseline and follow-up will be carried out at the Unit of Clinical Nutrition of the Careggi University Hospital, Florence, Italy, by study staff. All subjects will be examined between 7:30 am and 10:30 am after a 12-h fasting period. The standardized assessment at baseline for the intervention and control groups will include a questionnaire regarding demographic information, risk factors, and comorbidities. In addition, during the baseline visit, participants will be educated about the objectives and methods of the clinical study. Sessions for all participants will be similar in duration and content, except for details about diet; nutritionists will be instructed not to comment in favor of one diet over the other or indicate their eating habits.

Height will be measured with a stadiometer, while weight will be assessed with a professional weighing scale with 0.1-kg accuracy (TANITA, model TBF-410). BMI will be calculated as weight (kg)/height (m)^2^. Body composition will be determined with a bioelectrical impedance analyzer (Akern, model SE 101) at baseline and at follow-up visits. Blood samples will be collected at the beginning and end of each intervention phase. Blood samples will be centrifuged at 3000 rpm for 15 min, aliquoted to obtain serum, and stored at – 20 °C until analysis. The following biochemical measures will be evaluated: complete blood count, lipid profile (total cholesterol, LDL cholesterol, HDL cholesterol, triglycerides), fasting glucose, liver function tests (aspartate aminotransferase (AST), alanine transaminase (ALT), gamma-glutamyl transferase (γGT), renal function tests (serum creatinine, urea, uric acid), mineral profile (sodium, potassium, magnesium, calcium), iron metabolism (iron, ferritin), and vitamin profile (vitamin B12, folic acid).

Stool samples (four or five scoops totaling 4 g) will be collected before and after each intervention. Stool sample collection kits, including containers, will be provided to each participant. Fecal microbiota profiles and SCFAs (acetic, butyric, isobutyric, propionic, valeric, and isovaleric acids) will be evaluated. Total microbial DNA will be extracted from the faces by repeated scouring. The V3 and V4 hypervariable regions of the 16S rRNA gene for bacteria and ITS1-4 for fungi will be sequenced on the Illumina MiSeq platform, following the Illumina protocol for preparing 16S metagenomic sequencing libraries. SCFAs will be extracted using aqueous NaOH containing an internal standard. After extraction, an aliquot of supernatant fecal water will be derivatized with a propanol/pyridine mixture. The organic extract will be analyzed by gas chromatography-mass spectrometry (GC–MS) using deuterated internal standards and an appropriate GC Wax column.

Plans to promote participant retention and follow-up completion include the use of behavior change strategies such as self-monitoring and availability of study staff for any dietary counseling. In addition, participants will be contacted once during the study period to promote dietary compliance. A nutritionist will call unannounced, and each participant will recall his or her 24-h diet. At the end of the study, participants will be asked to fill out an adherence questionnaire in which they will indicate the extent to which they complied with the diets they received, their mealtimes and daily calorie distribution. They will also have to indicate whether and what kind of modifications they made to the diets they received and whether they encountered any difficulties.

If participants do not show up for the scheduled appointment, a maximum of three phone calls will be made and an e-mail will be sent before withdrawing the participant from the study. Participants who wish to prematurely discontinue the study before the 4-month evaluation will not undergo further clinical and laboratory evaluations. The reason for withdrawal will be documented in the participant’s record for later analysis when interpreting the results. The entire study will be discontinued if the observed results warrant premature discontinuation.

All data will be collected in an electronic database. Data or other identifiable documents will not be recorded in the database, and participants will be identified only by a unique study identification number. Hard copies of the files linking the participant identification number to the person’s contact details will be stored securely in a locked file cabinet in a locked office, accessible only to key members of the research team. Participant files and other source data (including copies of protocols, questionnaires, original test result reports, correspondence, informed consent records, and other documents related to the conduct of the study) will be retained for the maximum period allowed by the institution. The data will be made available upon request after publication.

Several strategies will be used to improve data quality during collection, including careful recruitment, a structured and time-limited protocol, inclusion of a run-in period, limiting the burden and inconvenience of data collection for participants, developing a trusting and collaborative relationship between research units and participants, and double data entry. Storage of biological samples will be under appropriate conditions according to standard methods. Blood samples will be aliquoted and stored at – 20 °C for 4 years before being used or destroyed. Preserved samples will be used only for research purposes with the consent of the donor. Destruction of samples will be properly documented.

### Statistical analysis

Statistical analyses will be performed using SPSS software for Macintosh (SPSS Inc., Chicago, IL, USA). Data will be analyzed using intention-to-treat and on-treat procedures. The primary outcome (change in body weight) will be analyzed within each group using Student’s *t*-test for paired data. The difference in absolute change (mean value at baseline subtracted from the mean value after the intervention for each subject) will be estimated using the Student’s *t*-test for independent data. Evaluation of distributions and checking for outliers will be performed using histograms and box plots. If appropriate, variables will be logarithmized to normalize the distributions of data. Continuous variables that follow a normal distribution will be summarized using the mean and standard deviations. Categorical variables will be presented in terms of frequencies and percentages. After testing the regression assumption, a general linear model for repeated measurements with adjustments for possible confounding factors will be run to compare the effects of different interventions. Data for the general linear model will be reported as geometric means and 95% confidence intervals. The same analyses will be performed for secondary outcomes. Subgroup analyses will be performed to analyze possible differences in the changes, according to some characteristics of the study population, such as age and gender.

Before starting the data analysis, the level and possible causes of missing data will be investigate using appropriate tables. This information will be used to determine whether the level and type of missing data have the potential to introduce bias into analysis results or substantially reduce the precision of the estimates for the proposed statistical methods. Sensitivity analyses will be performed, based on the assumption that the missing outcomes are the worst or best possible in the different randomization groups. If these show that the conclusions may differ based on the missing values, further multiple imputation will be performed for the missing values. These analyses will consider the results of any losses at follow-up to the extent that they relate to differences in the measured variables (i.e., under the assumption of random missingness). A *P* value < 0.05 will be considered statistically significant.

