### Outcomes

The primary outcome is weight change from baseline. Secondary outcomes are (1) body mass index (BMI) and fat mass change from baseline; (2) lipid and glycemic profile change from baseline (total cholesterol, LDL-cholesterol, HDL-cholesterol, triglycerides, fasting glucose); and (3) fecal microbiota profile and short-chain fatty acids (SCFAs) change from baseline. Body weight will be measured as a unique and established quantitative primary outcome, while assessment of body composition, biochemical profile, and gut microbiota will provide information on the cardiometabolic status of participants. The metric used will be the change in mean values from the beginning to the end of each dietary intervention.

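### The trial is sized on percent weight loss, tests absolute weight change and reports its adjusted model as geometric means, so the stated power does not belong to the stated test

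*Protocol article*

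**What the plan says.** Four statements in the protocol article bear on the scale of the primary outcome.

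- **Outcomes:** "The primary outcome is weight change from baseline". No unit or percent scale is given. The section adds: "The metric used will be the change in mean values from the beginning to the end of each dietary intervention".
- **Sample size:** the trial is powered for "a 1.4% weight reduction difference between the intervention group and the control group", with an SD of 0.4% and 22% loss to follow-up, leading to 54 per group. The Discussion repeats the 1.4% as the difference the study was designed to show.
- **Statistical analysis, t-test:** "The difference in absolute change (mean value at baseline subtracted from the mean value after the intervention for each subject") is compared between arms by an independent-samples t-test. Under Data collection and management, weight is measured on a scale accurate to 0.1 kg, so the absolute change is in kilograms. The unit is inferred, but securely.
- **Statistical analysis, model:** variables will be log-transformed where appropriate. A general linear model for repeated measurements, adjusted for possible confounders, then compares the interventions. Its reporting rule has no condition: "Data for the general linear model will be reported as geometric means and 95% confidence intervals". The same analyses apply to the secondary outcomes.

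**The concern.** A power statement holds for one variable and one test. Here the effect size and SD are in percent of baseline weight, while the test is on a difference that is not divided by baseline weight. Percent change is not named in Outcomes or in Statistical analysis.

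The adjusted model adds a third scale. If weight is not log-transformed, the model yields arithmetic means and the reporting rule does not fit it. If weight is log-transformed, the model yields a ratio, which is not the absolute difference in the t-test. Neither route matches the primary comparison.

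The risk is a choice of result after the fact. Eligibility is BMI of 25 or more with no upper limit, and the calorie rule expects participants on both sides of 90 kg, so the same percent loss corresponds to quite different kilogram losses. A report could then lead with percent, kilograms or a ratio, whichever is significant, and cite the protocol in support.

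**Working it through.** **1. The plan's own figure.** Inputs from Sample size: difference 1.4%, SD 0.4%, two-sided alpha 0.05 (sidedness assumed), power 0.80, loss 22%, stated result 54 per group.

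n per group = 2 × [(1.960 + 0.842) × SD / difference]² = 2 × (2.802 × 0.4 / 1.4)² = 1.28, rounded up to 2, or 3 after dividing by 0.78.

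The 54 is not reproduced. This is a separate matter from the scale problem, but it means that the stated SD cannot be used to compare scales. Solving the formula for the SD that gives 54:

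- All 54 evaluable: SD = (1.4 / 2.802) × √(54/2) = 2.60%.
- 54 enrolled, 54 × 0.78 = 42.1 evaluable: SD = (1.4 / 2.802) × √(42.1/2) = 2.29%.

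**2. What 1.4% means in kilograms.** Multiplying by baseline weight: 0.014 × 70 = 0.98 kg; 0.014 × 90 = 1.26 kg; 0.014 × 130 = 1.82 kg. Percent and absolute change are therefore different variables, not one variable in two units. No kilogram sample size can be computed, because the article gives no baseline weight mean or SD and no SD of the change in kilograms.

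**3. Can the two tests disagree?** This needs assumptions, so two data-generating models were simulated. Common to both: 58 completers per arm (75 × 0.78 = 58.5), baseline weight 85 ± 14 kg in women and 100 ± 16 kg in men, equal sexes, unadjusted t-tests at 0.05.

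| Assumed loss | Power, percent change | Power, absolute change | Trials where significance differs |
|---|---|---|---|
| Proportional to weight: mean 5%, SD 2.57%, difference 1.4% | about 83% | about 76% | about 11% |
| Constant in kg: mean 4.6, SD 2.36, difference 1.29 | about 74–76% | about 82–83% | about 12% |

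The kilogram inputs in the second row are the percent inputs at 92 kg: 0.05 × 92 = 4.6; 0.0257 × 92 = 2.36; 0.014 × 92 = 1.29.

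Under proportional loss with 42 completers per arm, SD 2.29%, mean baseline weight 88 kg (SD 15 to 20) and control-arm loss of 4 to 7%, power was 78–80% on percent and 61–73% on absolute change, with 10–23% of trials discordant.

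**4. The geometric-mean rule.** A repeated-measures model takes the weights at the two visits. These are positive, so geometric means exist. In one simulated arm they were 88.3 kg at baseline and 85.2 kg at the end, a ratio of 85.2 / 88.3 = 0.965. That is a relative change of about −3.5%. It is not the mean difference in kilograms, which is what the t-test estimates.

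**The case against.** Several points on the other side are sound.

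- **The outcome and the test agree.** Outcomes speaks of change in mean values and Statistical analysis tests absolute change. Only the sizing assumption is in percent, so restating it in kilograms would cure that mismatch without changing the outcome. This stands, and it is why the fix does not insist on percent.
- **Geometric means may be meant only for logged variables.** The preceding text makes logging conditional, and triglycerides and SCFAs are natural candidates. That is a likely intention, but the sentence as written has no such condition and follows directly on the model that compares the interventions.
- **A log-scale model lies close to the sizing scale.** This is true: the log-ratio had practically the same power as percent change in the proportional-loss simulations. It narrows the gap between model and sample size, but leaves the gap between model and t-test.
- **Adjustment reduces the disagreement.** Under proportional loss, adjusting kilogram change for baseline weight raised power to about 81% and cut discordance with percent to about 4%. The article plans an adjusted model but does not say that baseline weight is in it, and the t-test is unadjusted.

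Two stronger readings are tempting and should not be drawn. A reader might infer that the plan asks for a geometric mean of weight changes, which is undefined because most changes are negative. The document does not say that changes enter the model. A reader might also infer that the planned test is underpowered relative to percent change. That follows only if loss is proportional to weight; with loss constant in kilograms the order reverses.

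**Conclusion.** The point holds as an inconsistency of scale. The powered quantity is percent, the tested quantity is absolute, and the model's reporting rule is geometric whether or not the variable was logged. The first two parts rest on the document's words plus the inference that absolute weight change is in kilograms; the third rests on the missing condition in the reporting sentence.

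Its size can only be illustrated. At 58 per arm, significance differed between percent and absolute change in roughly 10 to 12% of simulated trials, given assumed baseline weights, an assumed SD near 2.6% and unadjusted tests. These runs show that the choice of scale can decide the conclusion. They do not show which scale is the more powerful.

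This should be corrected. It does not invalidate the design, and it is a stated rule that needs repair, not detail left to an analysis plan.

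**What to change.** Put the primary variable, its test and the sample-size assumption on one scale in Outcomes, Sample size and Statistical analysis. Either of these would do:

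- Name percent change from baseline as primary, as sized, and keep kilograms as supportive.
- Keep absolute change as primary, and restate the sizing difference and SD in kilograms with the baseline weight they assume.

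In both cases, report the adjusted arithmetic mean difference between arms with its 95% CI for weight, and limit geometric means, shown as between-arm ratios, to variables analysed on the log scale. The restatement of 1.4% in the Discussion should follow the scale chosen.

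No new data or visits are needed. The cost is that one weight scale becomes supportive and that an amendment is required, which under Oversight and monitoring goes to the Ethics Committee first. Recruitment began in March 2023, so the choice should be made and dated before anyone sees outcomes by arm. The kilogram option also needs a source for the SD of weight change, which the article does not give.
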